## 4.2 Calculation of Secondary Outcomes

### CGM Metrics

Each of the sensor glucose metrics listed above will be calculated over 24 hours unless otherwise noted. The metrics will be calculated based on up to 14 days of blinded CGM at 3-month intervals. Specifically, participants in both trial arms will be fitted with a blinded glucose sensor at study visit 2, which will be used to calculate baseline CGM metrics for each participant. Thereafter, participants in both arms will be fitted with blinded glucose sensors at 3, 6, 9, 12, 15, 18, 21, and 24 months post diagnosis of T1D. Additionally, subjects who opt to participate in the extension phase of the study will be fitted with a blinded sensor at months 36 and 48. A single percentage will be calculated for each subject at each of these visits by pooling all blinded CGM readings corresponding to the 14 day period. Similarly, baseline CGM metrics will be calculated using up to two weeks of CGM data fitted at study visit 2.

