## 5 Description of Statistical Methods

### 5.1 General Approach

This is an open-label, multi-center, single-period, randomized, parallel group design study of participants aged 10 to <17 years. It is expected that a total of up to 190 subjects will be recruited within ten working days of diagnosis of type 1 diabetes (T1D) through pediatric diabetes centers in the UK. Half of the participants will be treated by conventional multiple daily injection therapy (MDI) and the other half by closed loop insulin delivery system (CL). Initiation of treatment arm occurs at study visit 5 and will last 24 months. Additionally, subjects will have the option to participate in an extension phase that will go until 48 months.

The study includes up to 14 visits and 1 telephone/email contact for subjects completing the study. For subjects completing the extension phase, it will include an additional 3 visits and 6 contacts. After initiation of the treatment arm, visits will be conducted every 3 months in both arms during the main study and the optional extension phase. Beta-cell function will be assessed by serial measurement of C-peptide in response to a standardized MMTT. MMTTs will be conducted at baseline, 6, 12, and 24 months post diagnosis.

All analyses will compare the CL arm with the MDI arm and will follow the intention-to-treat principle with each participant analyzed according to the treatment assigned by randomization regardless of actual CL utilization. All randomized participants who have at least one CGM reading during the 24 month study period will be included in the secondary analyses of CGM metrics. For secondary analyses of CGM metrics after 24 months, only subjects with at least one reading occurring during the extension phase (i.e. after the date of the 24 month visit) will be included. The primary analysis will include all randomized participants.

All covariates obtained on a continuous scale will be entered into the models as continuous variables, unless it is determined that a variable does not have a linear relationship with the outcome. In such a case, categorization and/or transformation will be explored. All p-values will be two-sided.

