| 15 months | Days 421 to 480   |
| 18 months | Days 510 to 570   |
| 21 months | Days 600 to 660   |
| 24 months | Days 661 to 780   |
| 27 months | Days 781 to 840   |
| 30 months | Days 870 to 930   |
| 33 months | Days 960 to 1020  |
| 36 months | Days 1021 to 1140 |
| 39 months | Days 1141 to 1200 |
| 42 months | Days 1230 to 1290 |
| 45 months | Days 1320 to 1380 |
| 48 months | Days 1381 to 1500 |

245

246 These windows do not apply to the CGM metrics, which are calculated as described above.

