|                                             | *Visit 11         | HbA1c, data download, blinded CGM                                                                                                                                | After 18 months of diagnosis ( $\pm 2$ weeks)                                                      | <1 hour   |
|                                             | *Visit 12         | HbA1c, data download, blinded CGM                                                                                                                                | After 21 months of diagnosis ( $\pm 2$ weeks)                                                      | <1 hour   |
|                                             | *Visit 13         | Blinded CGM, sleep quality assessment                                                                                                                            | Between Visit 12 and Visit 14 (Visit 13 may coincide with visit 14)                                | <0.5 hour |
|                                             | Visit 14          | End of closed loop treatment: MMTT, HbA1c, data download, bloods for immunological analyses, questionnaires, computerised cognitive testing, focus groups        | After 24 months of diagnosis ( $\pm 2$ weeks)                                                      | 4-5 hours |

|                                         |           |                                                                         |                                               |           |
|-----------------------------------------|-----------|-------------------------------------------------------------------------|-----------------------------------------------|-----------|
| Optional extension phase
(24 months) | Contact   | Review use of study devices, HbA1c, study update                        | 3 months after Visit 14 ( $\pm 2$ weeks)      | <0.5 hour |
|                                         | Contact   | Review use of study devices, HbA1c, study update                        | 6 months after Visit 14 ( $\pm 2$ weeks)      | <0.5 hour |
|                                         | Contact   | Review use of study devices, HbA1c, study update                        | 9 months after Visit 14 ( $\pm 2$ weeks)      | <0.5 hour |

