|                                         | Visit 15  | Fasted C-peptide and glucose, HbA1c, blinded CGM, questionnaires        | After 36 months of diagnosis ( $\pm 2$ weeks) | <1 hour   |
|                                         | Contact   | Review use of study devices, HbA1c, study update                        | 3 months after Visit 15 ( $\pm 2$ weeks)      | <0.5 hour |
|                                         | Contact   | Review use of study devices, HbA1c, study update                        | 6 months after Visit 15 ( $\pm 2$ weeks)      | <0.5 hour |
|                                         | Contact   | Review use of study devices, HbA1c, study update                        | 9 months after Visit 15 ( $\pm 2$ weeks)      | <0.5 hour |
|                                         | *Visit 16 | Blinded CGM                                                             | 2 weeks before Visit 17 ( $\pm 2$ weeks)      | <0.5 hour |
|                                         | Visit 17  | Fasted C-peptide and glucose, HbA1c, blinded CGM review, questionnaires | After 48 months of diagnosis ( $\pm 2$ weeks) | <1 hour   |
| * could be done at home                 |           |                                                                         |                                               |           |

**Table 2: Schedule of study visits / phone contacts when the participant is randomised to standard therapy i.e. multiply daily injections (control group)**

|                                                    | Visit/
contact | Description                                                                                                                 | Start relative to
previous / next
Visit / Activity                                           | Duration  |
|----------------------------------------------------|-------------------|-----------------------------------------------------------------------------------------------------------------------------|----------------------------------------------------------------------------------------------------|-----------|
| Run in period                                      | Visit 1           | Recruitment and screening visit: Consent/assent; inclusion, exclusion; screening blood sample                               | Within 21 days of diagnosis                                                                        | 2-hours   |

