Additionally, participants will be fitted with the Actiwatch wristwatch, and the Pittsburgh Sleep Quality Index (PSQI) and a sleep diary will be handed out (details re sleep assessment see section 12.2.3) for assessment of sleep. The wristwatch will be worn for 7 days. Concomitantly, a sleep diary will be kept, and the PSQI will be completed by the participants (assisted by their parents/carers if need be), and their parents/carers.

All devices (blinded CGM, wristwatch) and the completed sleep diary and questionnaires, along with the blinded CGM device will be returned to the research team once the sensor life has expired and/or the sensor has detached, or at the end of study visit (Visit 14) at latest.

For those participants continuing with the extension phase, this visit can be combined with Visit 14.

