## 9.13 Transition to usual care

Following visit 14, for those not wishing to continue in the extension phase, (or following Visit 17 for those completing the extension phase) subjects randomised to closed loop will revert to conventional insulin therapy by switching back to either insulin pump alone or multiple daily injection therapy as per decision of the clinical team. Refresher training sessions on standard therapy will be provided by the routine clinical team to facilitate transition to usual care over a period of up to 8 weeks. During this period, subjects will be able to continue using the study insulin pump and/or study CGM (but not closed-loop) as required to facilitate transition. Subjects of the control intervention will continue with standard therapy as before.

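### At 48 months the blinded CGM window can include readings taken after closed loop has been withdrawn, and the SAP has no cut-off to remove them

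*Combined protocol and SAP*

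**What the plan says.** **Analysis rules.** SAP 4.2 (CGM Metrics) gives each participant a single value per visit, obtained "by pooling all blinded CGM readings corresponding to the 14 day period". For the extension it says only that sensors are fitted at months 36 and 48. SAP 7.1 sets analysis windows for the other outcomes, then adds: "These windows do not apply to the CGM metrics, which are calculated as described above". SAP 5.1 analyses participants as randomised, "regardless of actual CL utilization". For CGM analyses after 24 months, it says "only subjects with at least one reading occurring during the extension phase (i.e. after the date of the 24 month visit) will be included".

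**When closed loop ends.** Under protocol 9.13, after Visit 14 (participants not extending) or Visit 17 (participants completing the extension), "subjects randomised to closed loop will revert to conventional insulin therapy". For up to 8 weeks they may keep the study pump and/or CGM, but not closed loop. The control arm carries on unchanged. Section 9.14.2 confirms the change at Visit 17.

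**When the 48-month sensor is worn.** The protocol gives differing accounts:

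- Section 9.14.2: applied two weeks ahead of Visit 17, at Visit 16.
- Tables 1 and 2: Visit 16 is "2 weeks before Visit 17" with a tolerance of plus or minus 2 weeks. Visit 17 includes a review of the blinded CGM.
- Synopsis, Extension Phase row: sensors are fitted when the 36- and 48-month visits finish.
- Section 12.1.3.1: in the extension, the sensor is worn after each 12-monthly visit.

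**When the 24-month sensor is worn.** Table 1 times Visit 13 as "Between Visit 12 and Visit 14 (Visit 13 may coincide with visit 14"), and Table 2 also allows the two visits to coincide. Neither row limits who may do so. Section 9.11 does. It asks for attendance at least 2 weeks before Visit 14 and return of devices by Visit 14 at the latest, and says: "For those participants continuing with the extension phase, this visit can be combined with Visit 14".

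**The concern.** The 48-month CGM metrics are meant to compare closed loop with injection therapy at the end of four years. If part of the wear falls after Visit 17, part of the closed-loop arm's value describes conventional therapy begun because the study ended. The control arm has no such change, so the effect is one-sided.

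Nothing in the SAP would remove these readings. SAP 4.2 pools the whole wear and the visit windows do not cover CGM. The per-protocol rule in SAP 5.2 (closed-loop use at least 60% of the time) selects participants, not readings.

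At stake are the 48-month time in range, time below 3.9 mmol/L and other CGM secondary endpoints, and the 48-month per-protocol analysis of time in range. The exploratory plots of CGM metrics against closed-loop use (SAP 14.3) would also be affected. The 36-month sensor is not, because closed loop continues after Visit 15.

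**Working it through.** The plan states no figure for this point, so there is none to reproduce. The check is a day count followed by an illustration.

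**1. Inputs.** Closed loop stops on day 0 = Visit 17 (protocol 9.13, 9.14.2). Wear lasts up to 14 days (9.14.2); a full 14 days is taken here. Fitting day f runs from -28 to 0 (Visit 16 rows of Tables 1 and 2: nominal -14, plus or minus 14).

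**2. Days off closed loop** = max(0, f + 14); share s = days / 14.

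| Fitting day f | Days off closed loop | Share s |
|---|---|---|
| -28 | 0 of 14 | 0% |
| -14 (nominal, and 9.14.2) | 0 of 14 | 0% |
| -10 | 4 of 14 | 29% |
| -7 | 7 of 14 | 50% |
| -3 | 11 of 14 | 79% |
| 0 (latest permitted; also the synopsis wording) | 14 of 14 | 100% |

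**3. Average share, under an assumption.** If fitting were spread evenly over the 29 permitted days, the mean share would be (1 + 2 + ... + 14) / 14 / 29 = 7.5 / 29 = 26% (25% treating time as continuous). The documents do not say how fitting dates are distributed.

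**4. Effect on a between-arm difference, as an illustration.** Let D be the difference on closed loop, p the share of closed-loop participants fitted late, s their off-closed-loop share, and r the part of the advantage kept after withdrawal. The observed difference is D x [1 - p x s x (1 - r)].

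For D in time in range, the protocol's background offers 11 points (adults, section 4.2.7) and 72 - 53 = 19 points (adolescents, section 4.2.6). Both are against sensor-augmented pump therapy, not injections, so they only set a scale.

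- p = 0.25, s = 0.5, r = 0: 11 x 0.875 = 9.6 and 19 x 0.875 = 16.6 points.
- Same p and s, r = 0.5: 11 x 0.9375 = 10.3 and 19 x 0.9375 = 17.8 points.
- Even spread (mean share 0.25 across the arm), r = 0: 11 x 0.75 = 8.25 and 19 x 0.75 = 14.25, a loss of 2.75 to 4.75 points.
- Everyone fitted at Visit 17, r = 0: the difference is 0.
- Everyone fitted at the nominal date: no loss.

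**5. The same count at 24 months**, with day 0 = Visit 14. Participants leaving at Visit 14 are fitted on or before day -14 under 9.11, so max(0, -14 + 14) = 0 of 14 days. Those extending may be fitted at Visit 14 but stay on closed loop (9.14), so they also have 0 of 14. Only the Visit 13 table rows, read without 9.11, would give a leaver up to 14 of 14.

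**6. Eligibility for the post-24-month analyses.** A participant with a combined Visit 13/14 wears the 24-month sensor after the 24-month visit date. Those readings alone meet the SAP 5.1 condition, even with no 36- or 48-month sensor.

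**The case against.** **The intended timing avoids the problem.** Visit 16 exists to fit the sensor two weeks early, 9.14.2 says so, and a CGM review at Visit 17 makes sense only if wear is complete. This stands as far as it goes: at the nominal date no day is off treatment, so the plan *can* include such readings but does not necessarily do so. It does not remove the point, because the tolerance reaches Visit 17, two other places put the wear at the end of or after the visit, and no analysis rule enforces the intention.

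**Intention to treat covers it.** SAP 5.1 counts participants whatever their closed-loop use. That principle keeps people who stop during the assigned treatment period. Here the protocol itself ends that period for the whole arm, and later readings belong to neither assigned strategy.

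**The size is unsupported.** Largely right. An even spread of fitting dates and total loss of benefit are assumptions. After withdrawal participants may keep the pump and/or CGM, so they need not resemble the injection arm.

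**Stronger readings that a reader might infer.** One is that the 24-month metrics are contaminated too. Section 9.11 rules this out through its timing, device return and restriction on combined visits. A second is that time below 3.9 mmol/L is pulled toward no difference. The documents do not support a direction: the adolescent day-and-night study and the 17-adult study (sections 4.2.6 and 4.2.7) report time in or near that range as comparable between treatments. A third is that SAP 5.1 moves 24-month readings into the extension phase. It decides which participants enter; SAP 4.2 ties readings to a visit.

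**Conclusion.** The point holds for 48 months. As written, the plan permits between 0 and 14 of the 14 CGM days to fall after closed loop has ended, in one arm only, with no rule to exclude them. Dilution of the time-in-range and mean-glucose differences is the probable result, assuming that glucose control worsens at least partly once closed loop stops. Its size depends on actual fitting dates and on how much benefit persists, neither of which the documents give. The direction for hypoglycaemia metrics is unknown.

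The scope is limited to 48-month secondary, per-protocol and exploratory CGM results in participants who chose the extension. The C-peptide primary endpoint and the three key secondary endpoints are all at 12 months and are untouched.

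At 24 months two small matters remain: the Visit 13 rows omit the restriction in 9.11, and the SAP 5.1 eligibility rule can be met by a 24-month sensor.

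**What to change.** 1. **SAP 4.2:** compute the 48-month CGM metrics only from readings before the Visit 17 date, in both arms alike. Report the days of wear that contribute, by arm. This is needed even if scheduling is tightened, since 9.14.2 allows a replacement sensor, which could run past the visit.
2. **Protocol:** reconcile the synopsis (Extension Phase row), the Visit 16 rows of Tables 1 and 2, and section 12.1.3.1 with section 9.14.2, so that 48-month sensor wear finishes by Visit 17. The date on which closed loop ends is not in question.
3. **Tables 1 and 2, Visit 13:** carry over the restriction in 9.11 that only extension participants may combine Visits 13 and 14.
4. **SAP 5.1:** define eligibility for the post-24-month CGM analyses by having a 36- or 48-month sensor.

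The cost is a few lines of text. The downside is that some windows will be shorter than 14 days, and a participant fitted only at Visit 17 would have no usable 48-month CGM value; SAP 7.5 says that missing CGM data are not imputed. A sensitivity analysis using all readings would show whether the cut matters.

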## 7.3 Regression Modeling

At 12 months post diagnosis, a longitudinal analysis will be conducted for the primary outcome and each continuous secondary outcome using a linear mixed model with a random intercept and slope. For binary outcomes, a repeated measures logistic regression model will be used. All data collected up to and including the 12 month visit will be used to fit the models. The models will account for repeated measures coming from the same subject using an unstructured covariance matrix. They will adjust for baseline value, gender, presence or absence of DKA at diagnosis, and age as fixed effects, in addition to site as a random effect. If necessary, they may also adjust for HbA1c levels, BMI z-score, or race/ethnicity to assess for the presence of confounding. Residual values will be examined for an approximate normal distribution. If values are highly skewed, then a transformation or non-parametric methods will be used instead.

Using these longitudinal models, one treatment arm comparison will be performed specifically at 12 months for each metric and another treatment arm comparison will be performed combining data over all follow-up visits. The latter will be calculated using a linear contrast giving equal weight to each follow-up visit.

A composite analysis will not be performed for the lipid profile metrics, because they are not collected at any time points between the baseline visit and the 12 month visit (see table above).

An analogous longitudinal model will also be run at 24 months for each outcome metric, and at 36 and 48 months for subjects who participated in the extension phase.

In addition to the longitudinal models, boxplots will be used to display the distributions of the primary and secondary outcomes over time. If the longitudinal model produces a significant composite p-value for a particular outcome, then the boxplots will be used to explore the time at which the outcome began to differ between treatment arms.

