|                                             | Visit/
contact | Description                                                                                                                                                      | Start relative to
previous / next
Visit / Activity                                           | Duration  |
|---------------------------------------------|-------------------|------------------------------------------------------------------------------------------------------------------------------------------------------------------|----------------------------------------------------------------------------------------------------|-----------|
| Run in period                               | Visit 1           | Recruitment and screening visit: Consent/assent; inclusion, exclusion; screening blood sample                                                                    | Within 21 days of diagnosis                                                                        | 2 hours   |
|                                             | Visit 2           | Baseline visit: HbA1c, MMTT, blinded CGM, questionnaires, computerised cognitive testing, bloods for immunological analyses                                      | 7 to 21 days after diagnosis                                                                       | 3-4hours  |
|                                             |                   | Randomisation                                                                                                                                                    |                                                                                                    |           |
| Insulin pump
& CGM
Training           | Visit 3           | Insulin pump training, initiation study pump                                                                                                                     | Within 1 week of Visit 2                                                                           | 3-4 hours |
|                                             | Visit 4           | CGM training, initiation of CGM                                                                                                                                  | Within 0 to 7 days of Visit 3 (Visit 4 may coincide with Visit 3; Training visits can be repeated) | 2 hours   |

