## 9.3 Baseline visit (Visit 2)

Subject will arrive at the clinical facility in the morning at the agreed time. This session will include the following activities:

- Body weight measurement (see 12.1.1)
- Cognitive function will be assessed using validated computerized cognitive tests (see 12.2.2)
- A mixed meal tolerance test (MMTT) to assess residual beta cell function (see 12.1.2).
- In addition to measurements of C-peptide and blood glucose (MMTT), blood samples for analysis of HbA1c, lipid profile and immunological parameters will be taken (see 12.4)
- Validated questionnaires will be distributed to assess quality of life and diabetes management (see 12.2.1).
- At the end of this session, participants will be fitted with a blinded continuous glucose monitoring (CGM) device to assess baseline glycaemic control. Instructions on how to safely remove and send back the device will be provided (see 12.1.3.1)

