## 9.5 Randomisation

On completion of Visit 2, eligible subjects will be randomised in a 1:1 ratio using central randomisation software to the use of day and night closed loop or to standard therapy. The randomisation will be stratified by site, age, and possibly gender.

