### 14.2 Secondary analysis

#### 14.2.1 Biochemical evaluation

Secondary endpoints include trends over time in mean stimulated C-peptide AUC, fasting C-peptide, HbA1c levels, percentage of patients in each group with HbA1c <7.5% , insulin dose (U/kg), change in BMI standard deviation scores, change in blood pressure, and change in lipid profile. Based on CGM glucose levels during periods of blinded CGM sensors wear, the between group differences of the following parameter will be assessed: AUC less than 3.9mmol/l and 3.5mmol/l, time spent below target glucose (<3.9 mmol/l), time spent above target glucose (>10.0 mmol/l), time spent within the target glucose range (3.0mmol/l – 10.0 mmol/l), average, standard deviation, and the coefficient of variation of glucose levels, the time with glucose levels < 3.5 mmol/l, 3.0 mmol/l and <2.8 mmol/l, the time with glucose levels in the significant hyperglycaemia (glucose levels > 16.7 mmol/l), total, basal and bolus insulin dose. Trends in CGM and insulin data collected within intervention arms will be evaluated on a 3-monthly basis and on a 12 monthly basis during the extension phase. CGM and insulin data collected during intervention arms will also be compared to pre-intervention baseline CGM readings.

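### The baseline CGM window runs past study-pump start in the closed-loop arm, so adjusting for it can bias time in range and time below 3.9 mmol/L

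*Combined protocol and SAP*

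**What the plan says.** **Baseline CGM.** SAP 4.2 (CGM Metrics) states that "baseline CGM metrics will be calculated using up to two weeks of CGM data fitted at study visit 2". It pools all readings and sets no stop at randomisation or at device start.

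**Sequence.** Protocol 9.3 places sensor fitting last at Visit 2: "At the end of this session, participants will be fitted with a blinded continuous glucose monitoring (CGM) device to assess baseline glycaemic control". Protocol 9.5 then says "On completion of Visit 2, eligible subjects will be randomised in a 1:1 ratio using central randomisation software". In Protocol 9.1, Table 1, Visit 3 for the closed-loop arm is "Insulin pump training, initiation study pump", timed "Within 1 week of Visit 2". Visit 4, when real-time CGM starts, comes 0 to 7 days after Visit 3 and may be the same day. Controls stay on injections and receive extra training (Table 2; Protocol 9.6.2). SAP 5.1 and Protocol 9.7 place the start of the treatment arm at Visit 5.

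**Use.** SAP 7.3 says of the secondary-outcome models: "They will adjust for baseline value, gender, presence or absence of DKA at diagnosis, and age as fixed effects". SAP 13 tests time in range first, HbA1c second and time below 3.9 mmol/L third.

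**Stated purpose.** Protocol 12.1.3.1 describes the run-in recording as showing each participant's glucose control ahead of either treatment. Protocol 14.2.1 says that CGM and insulin data "will also be compared to pre-intervention baseline CGM readings".

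**Conflicting text.** The synopsis (Run in period) keeps everyone on injections after the baseline assessment, with core training for up to three weeks. Protocol 9.4 also puts a run-in of up to three weeks after that assessment. The overview in Protocol 9.1 puts run-in before randomisation. None of this fits a pump start within a week of Visit 2.

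**The concern.** A baseline covariate should be untouched by assignment. Here nearly all of the recording follows open-label randomisation, and much of it can fall after one arm has changed its method of insulin delivery. If that change moves glucose within days, the covariate carries part of the difference between arms, and adjustment subtracts it from the estimate.

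Two of the three key secondary endpoints are exposed. Time in range matters most because it leads a fixed sequence: if it fails, HbA1c and time below 3.9 mmol/L are not formally tested. The sequence runs at 0.05 if C-peptide is significant at 0.04, and otherwise at 0.01, where a lost point or two costs more.

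**Working it through.** The plan gives no figure for the CGM endpoints, so there is none to reproduce on this point. Its C-peptide sample size does reproduce (difference 0.126, SD 0.18: 43 per group by the normal formula, 43.9 by the t-based one, against 44 stated), but nothing below depends on it.

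**Step 1: calendar overlap.** Count days from Visit 2. Visit 3 is on day v3 (0 to 7), Visit 4 on day v4 (v3 to v3 + 7), and the sensor lasts w days (at most 14). The share of the window on the pump is max(0, w − v3)/w; replace v3 by v4 for real-time CGM. With w = 14:

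| Visit 3 day | Visit 4 day | Days on pump | Days on real-time CGM |
|---|---|---|---|
| 0 | 0 | 14 (100%) | 14 (100%) |
| 0 | 7 | 14 (100%) | 7 (50%) |
| 3.5 | 7 | 10.5 (75%) | 7 (50%) |
| 7 | 7 | 7 (50%) | 7 (50%) |
| 7 | 14 | 7 (50%) | 0 (0%) |

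Pump overlap is therefore 50% to 100%, and real-time CGM overlap 0% to 100%. Pump overlap depends only on the gap from Visit 2 to Visit 3, so it stands even if randomisation happened later than Protocol 9.5 says. A sensor lost before Visit 3 gives none.

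**Step 2: is closed loop running?** Protocol 9.7 sets Visit 5 relative to Visit 3 in wording that mixes a maximum with a minimum. Read as at least two weeks after Visit 3, Visit 5 falls on day v3 + 14, that is day 14 to 21 or later, outside the window. Read as a maximum, it could fall inside.

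**Step 3: effect on the adjusted difference.** The baseline-adjusted difference is (difference in outcome means) − b × (difference in baseline means), where b is the slope on baseline. If a share f of the closed-loop arm's window carries an early device effect d0, the baseline means differ by f × d0, so

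bias = −b × f × d0.

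This is the form for one follow-up visit. The SAP 7.3 mixed model has the same structure, with its own slope, on whatever scale is analysed. The documents give neither b nor d0, so both are assumed:

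- Central case for time in range: 0.4 × 0.5 × 5 points = 1.0 point.
- Low end: 0.3 × 0.5 × 2 = 0.3 points.
- High end: 0.7 × 1 × 10 = 7.0 points, which needs Visit 3 at essentially the time of Visit 2.
- No early device effect: 0.

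**Step 4: simulation check.** Assumptions: 44 per arm, 4,000 runs, true 12-month effect 10 points, SD 15, correlation 0.5 (so b = 0.5).

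| f | d0 | Formula | Simulated, adjusted | Simulated, unadjusted |
|---|---|---|---|---|
| 0 | 5 | 10.00 | 10.06 | 10.07 |
| 0.5 | 5 | 8.75 | 8.82 | 10.08 |
| 1 | 5 | 7.50 | 7.51 | 10.01 |
| 1 | 10 | 5.00 | 5.03 | 9.99 |

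**Step 5: what that does to power.** On the same assumptions the standard error is 15 × √(2/44) × √(1 − 0.25) = 2.77. At two-sided 0.01 (critical value 2.576), power is about 85% for an estimate of 10, 72% for 8.75 and 55% for 7.5.

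**Step 6: time below 3.9 mmol/L.** The formula is the same, but the documents give no sign for an early effect of pump and real-time CGM use. The direction is open.

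**The case against.** The strongest reply is that the tested treatment has not started. SAP 5.1 dates the arm from Visit 5, and on the likely reading of Protocol 9.7 that is day 14 or later, so calling the recording pre-intervention is defensible by the documents' own definition. This stands in part: a reader might infer that closed loop itself contaminates the baseline, and the schedule does not show that. But the study pump and real-time CGM are arm-specific changes, and the covariate is exposed to them.

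A reader might also infer that the recording starts after randomisation. It does not: the sensor is fitted just before, although almost all the data follow.

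The overlap is conditional on full wear and punctual visits, real-time CGM overlap is likely rather than certain, and the synopsis and Protocol 9.1 and 9.4 describe a different run-in. All of that is fair. The SAP, however, has no cut-off tied to device start, so nothing in it keeps pump-treated days out of the baseline.

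The size is modest too. One point compares with time-in-range differences of 19 points (72% against 53%, Protocol 4.2.6) and 11 points (Protocol 4.2.7) in earlier closed-loop studies, though in other populations and against sensor-augmented pump therapy. For time in range the likely harm is lost power, not a false claim. Visible imbalance in the baseline table cannot be claimed, since SAP 10 does not say that CGM metrics will appear there.

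**Conclusion.** The concern holds in limited form. The baseline CGM window begins immediately before randomisation, runs almost entirely after it, and with full wear and on-schedule visits puts 7 to 14 of 14 days in the closed-loop arm on the study pump. Adjusting for it can bias key secondary endpoints 1 and 3.

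For time in range the shift is toward the null if the early device effect has the same sign as the later one. It is about 1 point on the central assumptions and 0.3 to 7.0 points over the range tried; an early worsening would reverse it. For time below 3.9 mmol/L neither size nor direction can be stated.

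The documents do not support saying that the estimates are biased for certain, or that part of the treatment effect is removed from both endpoints. The C-peptide and HbA1c baselines are sampled at Visit 2, so the primary analysis and the second key endpoint are not affected.

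**What to change.** Before unblinded analysis:

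- **SAP 4.2.** Define baseline CGM in both arms as blinded readings before the date and time of Visit 3, with a pre-specified minimum number of hours. Report the hours contributed by arm, because Visit 3 is itself scheduled after randomisation.
- **SAP 7.3.** Where too little remains, keep the participant by modelling baseline as a response with a common mean across arms. This is a likelihood method, so it respects SAP 7.5, which does not impute CGM data.
- **Sensitivity analysis.** Omit the CGM baseline covariate and adjust for Visit 2 HbA1c instead.
- **Protocol.** Reconcile the run-in and randomisation sequence in the synopsis and in 9.1 and 9.4 with Table 1 and 9.5. Clarify the Visit 5 timing in 9.7. Align the wording in 12.1.3.1 and 14.2.1 with the window actually used.

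The cost is SAP text and a date filter on data already collected. The baseline becomes shorter (at most about 7 days) and noisier, with almost nothing left when Visit 3 is very early. As an upper bound on the precision lost, having no baseline covariate at all multiplies the standard error by 1/√(1 − ρ²): 1.05, 1.15 or 1.40 for an assumed baseline-to-outcome correlation ρ of 0.3, 0.5 or 0.7.
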